### Quality assurance

This protocol has been reviewed and revised several times by experts on acupuncture, orthopedics, statistics, and methodology. Before the trial, all the researchers will be requested to attend a series of training sessions, which will ensure that the personnel involved fully understand the trial protocol and standard operating procedures (SOPs) of the study. The data monitoring committee (DMC) will comprise the PI, CRC, and a researcher who will not be involved in the data collection aspect of this study. The DMC, which is independent from the sponsor and free from competing interests, will manage the data to ensure data validity. This study will be monitored by a clinical research associate (CRA), who will check all documents related to this study, including the case report forms (CRFs) and SOPs, and ensure that this clinical trial is conducted in accordance with the prescribed protocols and SOPs. Monitoring will be performed by an independent CRA, who will not be involved in any other aspect of the trial. In the event that the protocol described herein is revised, the revisions will require approval from the Ministry of Food and Drug Safety and the IRB of DongShin University Gwangju Korean Medicine Hospital.

### Sample size estimation

We had no preliminary study or adequate previous studies upon which to base sample size estimates. Therefore, we adopted a pilot study design. The appropriate sample size for two- or three-arm pilot studies is > 12 [35, 36]. Considering a dropout rate of 20%, we assigned 15 participants to each group (45 in total).

As our study is a pilot study, the sample size will not be sufficient for determining the efficacy of ILA for CLBP. Our study provides preliminary evidence for the efficacy and safety of ILA for CLBP.

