### Study design and setting

This manuscript was written in accordance with the SPIRIT (Standard Protocol Items: Recommendations for Interventional Trials) and CONSORT (Consolidated Standards Of Reporting Trials) 2010 guidelines [22, 23] (Additional file 1).

This study was a prospective, patient-blinded, parallel-arm, single-center (DongShin University Gwangju Korean Medicine Hospital, Republic of Korea), pilot randomized controlled clinical trial with a 1:1:1 allocation ratio. A total of 45 participants who met the inclusion criteria will be randomly allocated to the control, 650-nm ILA (650 ILA), or 830-nm ILA (830 ILA) group (*n* = 15 in each group). Participants in the control group will receive sham ILA for 10 min and real electroacupuncture (EA) for 10 min, while those in the 650 and 830 ILA groups will receive real ILA (i.e., 650 ILA group, 650-nm wavelength; 830 ILA group, 830-nm wavelength) and real EA both for 10 min. Participants will receive treatment once/day, twice/week for 4 weeks, at bilateral Shenshu (BL23), Qihaishu (BL24), Dachangshu (BL25), and Huantiao (GB30).

The primary outcome will be improvements in pain intensity assessed using the visual analog scale (VAS). The secondary outcome measures will include changes in scores in the Korean version of the Oswestry Disability Index (ODI) and the European Quality of Life Five Dimension Five Level scale (EQ-5D-5L). All scale scores will be recorded at baseline (before intervention), 4 weeks after the first intervention (i.e., at the end of the intervention), and 4 weeks after completion of the intervention.

This study protocol complies with the principles of the Declaration of Helsinki and Korean Good Clinical Practice guidelines and was approved by the Ministry of Food and Drug Safety (Medical Device Clinical Trial Plan approval No. 1039). The trial was registered with the Clinical Research Information Service (registration No. KCT0004610; registration date: January 7, 2020; http://cris.nih.go.kr). The study design is summarized in Figs. 1 and 2.

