### Statistical analysis

A statistician not involved in data collection will analyze the final data. We will perform a full analysis set (FA group) to assess the efficacy and a supplementary per-protocol analysis (PP group). We will compare the results of the statistical analyses between the FA and PP groups and confirm any statistically significant differences between the groups. If a significant difference exists between the PP and FA groups, the cause will be reviewed and reflected in the efficacy assessment. Missing values will be obtained using the “last observation carried forward” method. Interim analyses will not be performed. All statistical analyses will be performed using the SPSS version 21 software.

Baseline characteristics will be described and compared between the groups. Continuous data will be presented as means and standard deviations and compared using the independent *t* test or Mann-Whitney *U* test (nonparametric test). Categorical data will be presented as frequencies and percentages and compared using the chi-square or Fisher exact test.

Within each group, changes in VAS, ODI, and EQ-5D-5L scores at 4 weeks (the end of intervention) and 8 weeks (4 weeks after the end of intervention) after the start of intervention, relative to the baseline score, will be analyzed using a paired *t* test or Wilcoxon signed rank test (nonparametric test). Trends over time and time-by-treatment interactions will be explored using repeated-measure analysis of variance. The degrees of changes in the VAS, ODI, and EQ-5D-5L scores at each time point between the groups will be evaluated using the independent *t* test or Mann-Whitney *U* test (nonparametric test). Subanalyses will be performed according to participant age. All reported *p* values will be two-sided, with 95% confidence intervals. A *p* value < 0.05 will be considered statistically significant.

A safety assessment will be performed for all AEs that will occur during the study period. The incidence of AEs and SAEs will be summarized by group and analyzed using the chi-square or Fisher exact test.

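### Fifteen per group with 20% dropout leaves exactly 12, but the stated pilot criterion is more than 12

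*Protocol article*

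**What the plan says.** All the figures are in the protocol article.

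- Sample size estimation explains why there is no formal calculation: "We had no preliminary study or adequate previous studies upon which to base sample size estimates". It therefore uses a pilot-study rule with two citations: "The appropriate sample size for two- or three-arm pilot studies is > 12".
- The next sentence applies the rule: "Considering a dropout rate of 20%, we assigned 15 participants to each group (45 in total").
- Study design and setting confirms the layout, a "pilot randomized controlled clinical trial with a 1:1:1 allocation ratio" with 15 in each group.
- Sample size estimation adds that the trial is too small to determine efficacy. The limitations paragraph of the Discussion attributes the small size to limited funding as well as to the lack of preliminary studies.
- Trial status says that recruitment has ended.

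**The concern.** The section states a criterion, a dropout allowance and a resulting size. A reader should be able to get from the first two to the third. With the strict inequality as printed, that is not possible: the assumed dropout brings each group down to the boundary value that the criterion excludes.

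What is at stake is whether the sizing statement is internally correct. The results report will probably repeat it, and anyone who checks 15 × 0.8 will see that the trial, as described, was planned to fall just short of its own threshold. No test, estimate or allocation depends on the difference between 12 and 13.

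**Working it through.** **Inputs, all from Sample size estimation unless noted**

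- Criterion: more than 12. The sentence does not say per group or after dropout. Both are inferred from the sentence that follows it.
- Dropout: 20%.
- Assigned: 15 per group, 45 in total, allocated 1:1:1 (also in Study design and setting).
- No effect size, standard deviation or power enters the calculation.

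**Step 1. Reproduce the plan's figure.** Formula: n assigned = n required / (1 − dropout).

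- With n required = 12: 12 / 0.8 = 15.0, so 15 per group and 3 × 15 = 45 in total. This matches exactly.
- The cruder inflation 12 × 1.2 = 14.4 also rounds up to 15.

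So the plan's size was built on a base of exactly 12.

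**Step 2. Check the criterion in reverse.** Formula: expected completers = n assigned × (1 − dropout).

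- 15 × 0.8 = 12.0 per group, and 45 × 0.8 = 36 in total.
- 12 is not more than 12.

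**Step 3. Apply the criterion as printed.** In whole participants, more than 12 means at least 13.

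- 13 / 0.8 = 16.25, rounded up to 17 per group, and 3 × 17 = 51 in total. That is 2 more per group and 6 more overall.
- The cruder inflation gives 13 × 1.2 = 15.6, so 16 per group and 48 in total.
- If the expected number need only exceed 12 without reaching 13, then 16 × 0.8 = 12.8 would do.

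None of these versions returns 15.

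**Step 4. Find the dropout that 15 per group can bear.** Keeping 13 of 15 allows 2 losses: 2 / 15 = 13.3%. The assumed 20% is 3 of 15.

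**Step 5. Test other readings of the criterion.**

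- If it applied to randomised participants, 15 would pass, but the dropout allowance would then have no purpose.
- If it applied to the trial as a whole, 45 would be unexplained.

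Only a per-group, after-dropout reading connects the two sentences, and under it the strict inequality fails.

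**The case against.** The strongest reply is that the size is right and one character is wrong. Because 12 / 0.8 is exactly 15, the authors evidently inflated a base of 12 and meant at least 12. On that reading no number changes. This is probably what happened. It does not make the printed sentence correct, and the cited sources are not at hand to show whether they say 12 or more than 12.

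A second reply is that the words per group and after dropout are not in the text. That is true, and they are an inference here. No other reading gives the dropout allowance a purpose.

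A third reply is that efficacy is assessed in a full analysis set, with the per-protocol set supplementary, and that "Missing values will be obtained using the “last observation carried forward” method". Some dropouts may therefore still be analysed, so the number contributing could exceed 12 per group. This lessens the practical effect. It does not repair the stated calculation, which deducts dropouts from the number assigned.

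Three stronger conclusions are tempting, and the documents do not support them.

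- A reader might calculate how likely it is that all three groups keep more than 12 and call the design very likely to fail. A dropout allowance is an adjustment to the expected number. The plan never promises a minimum in every group, so that is not a fair test of it.
- A reader might say that this rule is the sole basis for the sample size. The Discussion also cites limited funding.
- A reader might fault the section for not stating the precision of the estimates. A condensed article may leave that to the full protocol, so its absence is not an error here.

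**Conclusion.** The point holds as a minor error in the text. At the plan's own 20% dropout, 15 per group gives an expected 12 completers, one short of what the strict criterion requires. The strict criterion would need 17 per group (51 in total), whereas a criterion of at least 12 is met exactly by 15 per group (45 in total).

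This rests on two assumptions: the criterion is per group, and it applies after dropout. A reader might infer that the trial is too small for its purpose. The documents do not support that. The size matches a criterion of at least 12, the article already says that the trial cannot determine efficacy, and no power statement rests on the difference of one participant.

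**What to change.** Do not enrol more participants, since recruitment has closed. Check the two cited sources and change the sentence in one of two ways.

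1. If they support it, state the criterion as at least 12 per group after dropout. The 15 per group and 45 in total then follow exactly from 12 / 0.8.
2. If they do require more than 12, keep that wording and add that 15 per group satisfies it only when at most 2 of 15 (13.3%) drop out, so it is not met at the assumed 20%. Report this as a limitation.

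Either version should say explicitly that the figure is per group and after dropout. The cost is one sentence, carried into the results report. Enrolment, data and analysis are unaffected. Under the second option the sizing statement reads slightly less favourably.

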## Methods/design

### Aims

This study will investigate the efficacy of ILA in the treatment of CLBP by comparing the effects of different wavelengths of ILA (650 and 830 nm) in terms of improvements in pain intensity, functional status, and patient quality of life.

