### Hypothesis

The null hypothesis is that different wavelengths of ILA will provide similar improvements in pain intensity, functional status, and quality of life in patients with CLBP.

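### The plan says 45 participants cannot determine efficacy, but its aim, null hypothesis and p < 0.05 tests do not carry that limit

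*Protocol article*

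**What the plan says.** The Sample size estimation section explains that "We had no preliminary study or adequate previous studies upon which to base sample size estimates", adopts a pilot design, and relies on a rule of thumb: "The appropriate sample size for two- or three-arm pilot studies is > 12". After a 20% allowance for dropout this becomes 15 per arm. The section then states that "the sample size will not be sufficient for determining the efficacy of ILA for CLBP" and that the study gives preliminary evidence on efficacy and safety. The Discussion lists the small single-center sample as a limitation.

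Three other sections are worded without that limit:

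- **Aims:** "This study will investigate the efficacy of ILA in the treatment of CLBP", by comparing the two wavelengths on pain, function and quality of life.
- **Hypothesis:** the null is that "different wavelengths of ILA will provide similar improvements in pain intensity, functional status, and quality of life in patients with CLBP". No margin defines similar, and no null is stated for laser against sham.
- **Statistical analysis:** the full analysis set is used to assess efficacy. Changes in VAS, ODI and EQ-5D-5L are compared between groups at each time point by t test or Mann-Whitney test. All reported p "values will be two-sided, with 95% confidence intervals", and a p "value < 0.05 will be considered statistically significant". Only the repeated-measures analysis is described as exploring anything.

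**The concern.** An analyst works from the Statistical analysis section, and that section carries no caveat. Two misreadings become easy.

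1. If the comparison of 650 nm with 830 nm is not significant, a null worded as similarity is left standing. A reader may take this as evidence that the wavelengths are alike, although large differences remain possible.
2. If a comparison is significant, its estimate has passed through a filter that only large observed differences can pass, so on average it is too large. The protocol gives the lack of adequate earlier data as its reason for running a pilot, and the Discussion offers the results as a basis for further research. An inflated estimate would make the next trial too small.

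**Working it through.** **Inputs from the protocol.** Three arms at 1:1:1, 15 per arm, 20% dropout, two-sided 0.05, pairwise comparison of means. The protocol gives no effect size, SD or power.

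**Assumptions.** True differences of 0.3, 0.5, 0.8 and 1.0 SD; for conversion to millimetres, an SD of 15 to 25 mm on the 100 mm VAS. Here SD means the SD of the quantity compared.

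**Step 1: the plan's own figure.** Reading the rule of thumb as 12 completers per arm, 12 / (1 − 0.20) = 15 per arm, and 3 × 15 = 45. The stated size reproduces.

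**Step 2: precision.** Half-width of the 95% interval for a difference = t(0.975, 2n − 2) × √(2/n) × SD.

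- n = 15: 2.048 × 0.365 = 0.748 SD, or 11 to 19 mm.
- n = 12: 2.074 × 0.408 = 0.847 SD, or 13 to 21 mm.

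The observed difference must exceed these same values to reach p < 0.05.

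**Step 3: power and exaggeration.** Power is that of the two-sample t test (noncentral t, noncentrality d × √(n/2)). Exaggeration is the mean absolute estimate among significant results divided by the true effect, from 200,000 simulated trials per row.

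| True effect (SD) | Power, n = 15 | Power, n = 12 | Mean significant estimate, n = 15 (SD) | Exaggeration, n = 15 | Exaggeration, n = 12 |
|---|---|---|---|---|---|
| 0.3 | 12.5% | 11% | 0.88 | 2.9 | 3.2 |
| 0.5 | 26% | 22% | 0.94 | 1.9 | 2.1 |
| 0.8 | 56% | 47% | 1.05 | 1.3 | 1.4 |
| 1.0 | 75% | 65% | 1.15 | 1.15 | 1.2 |

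A true difference of 0.5 SD would be non-significant in 74% of trials with 15 per arm (1 − 0.26) and 78% with 12. At 15 per arm, 80% power needs a true difference of 1.06 SD.

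**Step 4: effect on the next trial.** The required size varies as 1/d². For 80% power a true 0.5 SD needs 63 per arm before dropout. Planning on the mean significant estimate of 0.94 SD gives 63 × (0.5/0.94)² ≈ 18. For a true 0.8 SD the figures are 25 per arm and 25 × (0.8/1.05)² ≈ 15.

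**Step 5: what baseline adjustment adds.** Let ρ be the correlation of baseline with week-4 VAS. A change score has variance σ₄² + σ₀² − 2ρσ₀σ₄. The baseline-adjusted residual variance is σ₄²(1 − ρ²), the smallest value that any fixed multiple of baseline can give, so it is never larger. With equal SDs the ratio is (1 − ρ²) / (2(1 − ρ)) = (1 + ρ)/2, below 1 whenever ρ < 1. The price is one degree of freedom.

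**The case against.** The strongest reply is that the protocol has already said this. The quoted sentence is its own caveat; the abstract and the Discussion also promise only preliminary evidence. Investigating efficacy and being unable to determine it can be read together. This stands: nothing was concealed, and the fault is only that the caveat was not carried into the sections that govern the analysis.

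Stronger readings are tempting, and the document does not support them:

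- **That p < 0.05 is a rule for declaring efficacy.** The sentence only defines the label statistically significant. Nowhere is an efficacy conclusion tied to it.
- **That a null result will be reported as similarity.** No section says so, and the word may be a loose way of writing no difference. The wording and the missing margin create a risk; they do not announce an intention.
- **That interval estimates are left out.** The Statistical analysis section already mentions 95% confidence intervals. What it does not do is make the between-arm interval the main result.
- **That any significant result will be badly inflated.** At 1.0 SD the exaggeration is only 1.15-fold.
- **That retention and attendance must become headline results.** The stated purpose is preliminary efficacy and safety, so this would be a preference about pilots.

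The figures also apply to any trial with 15 per arm, a size the protocol openly accepts. That is why the remedy concerns the framing and main estimate and does not ask for more participants.

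**Conclusion.** The point holds as a misalignment between sections. The sample size section sets a limit that the aim, the hypothesis and the testing plan do not carry. With intervals reaching 0.75 to 0.85 SD either side of the estimate, non-significance cannot support similarity of the two wavelengths. A significant estimate overstates the truth by a factor between about 1.15 (true effect 1.0 SD) and 2.9 (0.3 SD) at 15 per arm, so it should not size the next trial by itself.

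The half-widths in SD units rest only on the planned numbers and the t test. Power and exaggeration depend on the assumed true effect, and the millimetre figures on the assumed SD; the protocol gives neither. The data are not invalidated, and a reader should not infer that the trial needs to be larger. The correction is cheap and worth making because it decides how the results are read.

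**What to change.** - **Aims:** state the aim as preliminary estimation of the effects of the two wavelengths.
- **Hypothesis:** word the null as no difference.
- **Statistical analysis, main result:** replace the unadjusted tests of change with the baseline-adjusted (ANCOVA) difference in week-4 VAS, with 95% confidence interval, for 650 nm v control, 830 nm v control and 650 nm v 830 nm. This matches the primary end point named under Outcome measurements and uses data already scheduled.
- **Statistical analysis, interpretation:** label p values exploratory, and state that an interval containing zero is not evidence of similarity.
- **For the next trial:** report the week-4 VAS SD alongside the interval, so that planning does not rest on a significant point estimate alone.

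Cost: this is a small change of analysis method as well as of wording. Under Quality assurance, protocol revisions need approval from the ministry and the IRB. The Trial status section says recruitment has ended, so the change should be dated and made before the outcome data are analysed, or else declared as made afterwards. The report gives up a headline claim of significant efficacy. No new data or participants are needed.

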### Statistical analysis

A statistician not involved in data collection will analyze the final data. We will perform a full analysis set (FA group) to assess the efficacy and a supplementary per-protocol analysis (PP group). We will compare the results of the statistical analyses between the FA and PP groups and confirm any statistically significant differences between the groups. If a significant difference exists between the PP and FA groups, the cause will be reviewed and reflected in the efficacy assessment. Missing values will be obtained using the “last observation carried forward” method. Interim analyses will not be performed. All statistical analyses will be performed using the SPSS version 21 software.

Baseline characteristics will be described and compared between the groups. Continuous data will be presented as means and standard deviations and compared using the independent *t* test or Mann-Whitney *U* test (nonparametric test). Categorical data will be presented as frequencies and percentages and compared using the chi-square or Fisher exact test.

Within each group, changes in VAS, ODI, and EQ-5D-5L scores at 4 weeks (the end of intervention) and 8 weeks (4 weeks after the end of intervention) after the start of intervention, relative to the baseline score, will be analyzed using a paired *t* test or Wilcoxon signed rank test (nonparametric test). Trends over time and time-by-treatment interactions will be explored using repeated-measure analysis of variance. The degrees of changes in the VAS, ODI, and EQ-5D-5L scores at each time point between the groups will be evaluated using the independent *t* test or Mann-Whitney *U* test (nonparametric test). Subanalyses will be performed according to participant age. All reported *p* values will be two-sided, with 95% confidence intervals. A *p* value < 0.05 will be considered statistically significant.

A safety assessment will be performed for all AEs that will occur during the study period. The incidence of AEs and SAEs will be summarized by group and analyzed using the chi-square or Fisher exact test.

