### Dropout criteria

Participants will be dropped from the trial under the following conditions: (1) < 75% compliance with the protocol procedures (participating in < 6 of the 8 scheduled treatment sessions); (2) occurrence of a serious adverse event (SAE); (3) reluctance to continue the trial; (4) incomplete data that could influence the trial; (5) large errors in protocol or significant deviations in implementation; or (6) if the principal investigator (PI) or institutional review board (IRB) decides to terminate their participation in the trial.

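### The review of discrepancies between the full analysis and per-protocol sets depends on a significant difference between nested sets, a trigger that is unsound on either reading

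*Protocol article*

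**What the plan says.** All the analysis wording is in the protocol article, Statistical analysis. The two sets and their roles are given first: "We will perform a full analysis set (FA group) to assess the efficacy and a supplementary per-protocol analysis (PP group". Their comparison is described as follows: "We will compare the results of the statistical analyses between the FA and PP groups and confirm any statistically significant differences between the groups". The consequence is conditional: "If a significant difference exists between the PP and FA groups, the cause will be reviewed and reflected in the efficacy assessment".

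No test is named for this comparison. For VAS, ODI and EQ-5D-5L changes in the study arms, the differences "between the groups will be evaluated using the independent *t* test or Mann-Whitney *U* test (nonparametric test"). The general rule is that a *p* "value < 0.05 will be considered statistically significant", and *p* "values will be two-sided, with 95% confidence intervals".

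On the size of the sets, Sample size estimation says: "Considering a dropout rate of 20%, we assigned 15 participants to each group (45 in total"). Dropout criteria lists, among other reasons for removal, "< 75% compliance with the protocol procedures (participating in < 6 of the 8 scheduled treatment sessions"). The article does not tie these criteria to membership of PP.

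**The concern.** The FA and PP sets are not two groups of people. PP is ordinarily FA with some participants removed, so the two results share most of their data. A significance test that treats the sets as separate samples uses a standard error that is much too large. Comparing which set crosses 0.05 responds largely to the loss of a few participants and to chance, and not only to a change in the effect.

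This matters because the comparison is the article's stated check on whether exclusions alter the efficacy picture, and the review of cause, which feeds into the efficacy assessment, starts only when the trigger fires. Several removal criteria leave room for judgement (data incomplete enough to influence the trial, large protocol errors, a decision of the principal investigator), and the practitioners know the allocation. A trigger that seldom responds to selective exclusion would let it pass without review.

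**Working it through.** **Inputs.** From the article: 15 per arm, 45 in total, 20% dropout, two-sided 0.05. Assumed, because the article does not give them: PP is a subset of FA; the 20% dropout is also the share missing from PP; VAS change is normal with SD 1; excluded participants differ from the rest by 0 to 3 SD.

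**The plan's own figure.** 12 / (1 − 0.20) = 15 per arm, and 3 × 15 = 45, as stated. So 20% loss leaves m = 12 of n = 15 per arm, or 36 of 45 pooled.

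**Reading (a): FA and PP tested as two independent groups.**

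- If exclusions are unrelated to outcome, the true variance of (PP mean − FA mean) is s²(1/m − 1/n). For 12 of 15 this is s²(0.0833 − 0.0667) = 0.0167 s².
- An independent-sample test uses s²(1/m + 1/n) = s²(0.0833 + 0.0667) = 0.15 s².
- The test statistic therefore has SD √(0.0167 / 0.15) = 0.333 instead of 1. The ratio is the same for 36 of 45.
- The critical value of 1.96 becomes 1.96 / 0.333 = 5.88 true standard errors, so the actual size is about 4 × 10⁻⁹ instead of 0.05.
- If the excluded are δ SD worse, the mean moves by (3/15) × δ: 0.2, 0.4 and 0.6 SD for δ = 1, 2 and 3.

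Simulated rejection by the independent *t* test (40,000 trials per case):

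| Excluded worse by | Per arm, 15 v 12 | Pooled, 45 v 36 |
|---|---|---|
| 0 SD | 0% | 0% |
| 1 SD | 0% | 0% |
| 2 SD | 0% | 2.5% |
| 3 SD | 0% | 53% |

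The Mann-Whitney test gave 0% at 0, 1 and 2 SD in both layouts (5,000 trials). If 40% were missing from PP instead of 20%, the per-arm *t* test would reject in 0.01%, 0.7% and 7.8% at 1, 2 and 3 SD. Pooled, it would reject in 15%, 97% and 100%.

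**Reading (b): an arm comparison is significant in one set and not in the other.** Two arms of 15 were compared by independent *t* test, first in FA and then in PP (40,000 trials).

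- Three random exclusions per arm, so the true effect is the same in both sets: the verdicts differ in about 4% of trials at no effect, 12% to 13% at 0.5 SD and 17% at 0.8 SD.
- No true effect, three worst responders of one arm removed from PP: that arm's mean shifts by 0.33 SD. The false-positive rate is about 5% in FA and about 16% in PP. The verdicts differ in about 15% of trials.
- Benchmark for the last case, three random participants removed from that arm: the verdicts differ in about 3%.

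So under (b) the trigger rises from about 3% to about 15% when exclusions distort the result, but stays silent in about 85% of those trials. With a real effect and harmless exclusions it fires about as often.

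**The case against.** The strongest objection is that the article never says FA and PP will be compared with an independent-sample test. The listed tests are for the study arms, and a comparison of analysis results would ordinarily mean running the arm comparison in each set and looking at whether the conclusions agree. This stands: a reader might infer that the near-zero rejection rates describe the plan, but they describe only reading (a). The conditional sentence, with its difference between the PP and FA groups, leaves that reading open without settling it.

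It also stands that reading (b) is not blind. It responds to distortion (about 15% against 3%), and a false alarm costs only a review. That answers a claim that the check can never work, but not the complaint that it is weak and noisy.

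Testing excluded against retained participants is no remedy. That test has the right size, but it asks whether the excluded differ, not whether removing them moves the treatment contrast. If the excluded are equally worse in both arms, the contrast does not shift on average.

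Finally, set definitions and details of the comparison may properly sit in the full protocol or analysis plan, and their absence is no fault here. The point rests on the rule the article does state: action only on a significant difference.

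**Conclusion.** The concern holds as a defect in a stated decision rule. Significance between nested sets is an unsound trigger. Under reading (a) it is practically inert per arm at 12 of 15; pooled, it gains power only at extreme shifts or with far more exclusions. Under reading (b) it fires in about 4% to 17% of trials when exclusions are harmless and in about 15% when they clearly distort one arm.

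Three stronger conclusions are not supported. A reader might infer that the efficacy result is compromised; it is not, because FA carries efficacy, PP is supplementary, and the article itself says the pilot is too small to determine efficacy. A reader might infer that the authors will take non-significance as proof of robustness; the article does not say so, and its comparison of FA and PP results is unconditional, with only the cause review depending on significance. A reader might infer that the trigger carries no information; reading (b) carries some.

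The figures rest on normal data, the overlap of PP with FA, and the 20% dropout used as the PP exclusion rate. Severity is minor to moderate.

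**What to change.** In Statistical analysis, delete the search for a significant FA-PP difference and the conditional sentence after it. Replace them with wording such as: *The between-arm differences in VAS at the end of the intervention will be reported for FA and PP side by side, with 95% confidence intervals. The number of participants excluded from PP, the reasons, and their VAS change where observed will be tabulated by arm and reviewed whatever the p values. A non-significant comparison will not be taken as agreement between the sets.*

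Optionally, add a confidence interval for the FA-minus-PP shift in each between-arm difference, obtained by bootstrap resampling of participants within arm so that the overlap is respected.

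The cost is a few sentences and one small table, with no further participants or data. The bootstrap interval, if used, needs a little extra code and will be wide at this sample size.
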